**A randomized controlled trial comparing two protocols of shock wave therapy for patients with planter fasciitis.**

**By:**

**[name]**

**[name]**

# **CHAPTER I**

## **INTRODUCTION**

### **Background:**

Between 1995-2000, the number of patient visits to the outpatient departments was highly increasing, reaching around one million visits annually for the diagnosis and management of plantar fasciitis (PF). However, 19% of all visits were made for physiotherapy, 26% for exercises counseling and the other percentage was divided between pain medication and orthopedic surgeons in the National Hospital Ambulatory Medical Care **(Riddle et al., 2004)**.

The heel pain at the inferior and medial aspect of the calcaneus affects millions of people in the world. It is estimated that the prevalence of tenderness on palpation with foot pain related to the plantar fascia 6.4 for men and 7.2% for women. Similarly, the plantar heel pad was 4.3% for men and 3.9% for women. **(J. E. Dunn et al., 2004)**.

Furthermore, PF is considered as a common cause of heel pain which affects the patient's life. However, the plantar fasciitis impacts both genders but the percent of the incidence with women is slightly more than men as reported earlier. It is associated with sports but commonly reported with runners and approximately the percent of incidence is 5% - 10%. The high percent of incidence presents with runners and is considered normal due to the running's biomechanics. During running the vertical force of the foot against the ground can lead to double the body weight acting on the PF and foot arch which should be responsible for the absorption mechanism. However, the cost management of plantar fasciitis was estimated between 192-376 million in the United States **(Petraglia et al., 2017)**.

Most of the studies analyzed different treatments of plantar fasciitis including the shockwave but with no specific or fixed parameters set for the administration of the shockwave. It was previously demonstrated that shockwave therapy has a significant improvement in the pain that confirmed by using analog visual scale outcome which seen after three weeks without specifying the parameters of shockwave **(Leao et al, 2020)**.

Another study compared the effect of shockwave therapy and local corticosteroid injection on patients of plantar fasciitis that confirmed both of them contributes in decreasing the pain of plantar fasciitis but shockwave therapy given longer relief than the local corticosteroid injection. However, there is no identified a fixed parameters of shockwave in this study (Xu et al, 2020).

### **Statement of the problem:**

What is the difference between two protocols of shockwave therapy on planter fasciitis with regards improving function and decreasing the pain?

### **Purpose of the study:**

The purpose of this study is to compare the results of different protocol of extracorporeal shockwave therapy on improving function with plantar fasciitis and reducing the pain after 6 sessions of the intervention.

### **Delimitation:**

The study will be delimited to:

1. Patients with plantar fasciitis of both genders
2. The age will be ranged from 20 to 50 years old.
3. The patients should be able to understand and follow the verbal instructions.
4. The pain should be from moderate to severe.
5. Functional limitation from moderate to severe

### **Basic assumptions:**

1. All subjects will attend the assessment sessions
2. All the subjects will receive the intervention as established
3. The modality will be properly calibrated

### **Significance of the study:**

To provide evidence that both protocols are effectiveness but there is lacking in the previous literature about the difference between 2 protocols when using the shock wave when handling cases of PF.

Shockwave therapy is a safe and effective non-surgical treatment of plantar fasciitis comparing to other treatments. Moreover, the researchers recommend the use of shockwave therapy for plantar fasciitis.

This study may help physiotherapists to exclude using the slow acting devices and save the time by using a specific protocol of a fast effective modality in the treatment of PF.

### **Hypothesis:**

There will be a significant difference between different protocols of shockwave on function and pain in cases of PF.

## **CHAPTER II** **LITERATURE REVIEW**

The literature review of this study will be presented as follows:

1. Definition of plantar fasciitis.
2. The risk factors of plantar fasciitis.
3. Anatomy of plantar fascia.
4. The pathophysiology of plantar fasciitis.
5. Shockwave therapy

### **Plantar fasciitis:**

The plantar fascia is a thick band that connects the calcaneus bone to the forefoot. The plantar fascia absorbs the shock for pressure on the foot and helps in the walking by supporting the arch of foot. Consequently, the plantar fascia can be damaged because of the pressure during the daily life. Plantar fasciitis is a degenerative condition which is results from reparative micro tears in the fascia which lead to an inflammation in the insertion of the plantar fascia. The plantar fasciitis is the one of causes of heel pain and orthopedic complaints. The

pain actually in the bottom of the heel and sometime in the medial aspect of the heel (Luffy et al.,2018).

### **Risk factors :**

The risk factors of plantar fasciitis are divided to intrinsic and extrinsic. The intrinsic factors consist of anatomic factors such as (shortness of Achilles tendon, obesity, pes planus and pes cavus) , Also the biomechanics' factors considered part from intrinsic factors such as (restricted dorsiflexion of ankle, excessive foot pronation, weakness of intrinsic foot and plantar flexors muscles). So, the extrinsic factors consist of environmental factors such as (inappropriate shoes, walking on hard surface, barefoot , prolong standing/walking and poor alignment). All these factors can assessed by physiotherapist in the examination session that guides to appropriate treatment (Schwartz et al.,2014).

### **Anatomy:**

The plantar fascia (**Fig.1**) includes three bands of thickened fibrous aponeurosis, which are dividing depend on their location. The divided bands are the medial, central and lateral which is the central considers the thickest one and it stronger more than others. However, the plantar fascia originate at calcaneus tubercle from medial aspect and runs forward as fan shape to insert at each proximal phalanx which it dividing into five bands and continuing to forming the flexor sheaths of the toes. The plantar nerves are moves in and around of plantar fascia. The plantar fascia helps in stability of first metatarsophalangeal joint and arch during the Windlass Mechanism and helps in normal walking as well mainly thru heel rise (Thompson JV et al.,2014).

[figure not shown]

**Anatomy of the Sole of the Foot**

**Fig.1: Anatomy of the sole/plantar fascia**

### **Pathophysiology:**

Plantar fasciitis is a degenerative process including the thickened fibrous aponeurosis (plantar fascia) and most common site of degenerating is a medial side of calcaneus tubercle. The process is happen through the repetitive strain in the tissue which lead to micro-tearing of plantar aponeurosis. Furthermore, the histologic analysis confirmed that a calcification, chondroid metaplasia and collagen necrosis results the fibrosis and thickening of plantar fascia. Plantar fasciitis assumed to be an inflammation process, but the findings (thickening and fibrosis of plantar) suggested a degenerative mechanism. Depending on that, the authors suggested a plantar fasciosis could be more accurate term rather than plantar fasciitis (**Lemont H et al.,2003**).

### **Extracorporeal Shockwave Therapy (ESWT):**

Shockwave therapy considered a multidisciplinary modality that is use in different clinics such as (physiotherapy, orthopedics and sport medicine). So, Shockwave therapy is an non-invasive treatment of damaged soft tissue. In addition, it has other features like a safe, fast and effective treatment to relief the pain. However, the clinicians preferring to use it before the decision for surgery, injections and steroid medication to manage the pain and mobility restoration that is clinically confirmed to stimulate metabolic reactions. The shockwave therapy stimulate the enzymes and provoke an acute healing process which means activates the process of healing and decreasing the pain. All the application of shockwave therapy is an evidence-based and it is an effective treatment for many conditions such as plantar fasciitis, tennis elbow and Achilles, hamstring and gluteal tendons. Hence, the shockwave therapy works after determine the complaint area by the clinician after that should put some gel on the area then the shockwave device is apply. The shockwave device consist of hand piece and fast moving rocket which controlled by a compressor. The rocket transmits the force to the head that produce the shockwaves then move in and absorbs by the body. Addition to that the clinicians can adjust the frequency, impulse, pressure and time of wave (**Cheing et al.,2003**).

There are many studies talking about shockwave therapy in the treatment of PF. The researchers showed a significant clinical improvement of focused extracorporeal shockwave therapy in the treatment of PF without using anesthesia and confirmed between 50 – 65% of success rate (**Gollwitzer H et al, 2015**).

There is another study recommended to use shock wave therapy in the treatment of PF to any patient over 6 months. Moreover, it confirmed the significant improvement and no negative side effects have been reported from extracorporeal shock wave therapy. So, the results of this study revealed that shock wave therapy is useful, safe and effective with no negative side effects (**Rompe et al, 2003**).

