**Sample size estimation:**

A pilot study will be conducted to detect the effect size required (at alpha level of 0.05 and power of 0.8)

A priori power analysis will be performed (G\*power, version 3.1.9.3, Duesseldorf, Germany), based on previous studies on PF

Pain, considered the Primary outcome measure and revealing a visual analogue scale (VAS) of 4-10 on the pain scale for PF.

Function limitation considered the secondary outcome measure and exposing a Foot Function Index of 100/170 or at least 60%.

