#### Control group - C:

This group will receive the same physiotherapy program in addition to sham shock wave therapy

The pain and function improvement will be assessed before and after 6 sessions. An additional assessment will be performed at the end of the 12th week for a short follow-up

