### **Outcomes:**

- **Foot Function Index:**

The foot function index (FFI) is an outcome measure that has been used to measure the impact of foot pathology and it can be used in clinical and studies setting which related to foot disorders. FFI is a questionnaire consist of 23 self-

reported items and divided to sub-scales. The patient has to score him self in each question from 0 (no pain/disability) to 10 (worst pain/required help). The pain sub-scale consist of 9 questions that it measures the pain in different situation. The second sub-scale is a disability which consist of 9 questions and it measures the difficulty performing. The last sub-scale is activity limitation which consist of 5 questions and it measures the limitation or restriction of activities (**Budiman-Mak E et al, 1991**)

Additionally, the FFI is recommended as a validated and reliable outcome scale for using in foot pathologies intervention trails (**Saag KG et al,1996**).

- **Visual Analog Scale**

The pain will be assessed before and after the intervention by using visual analog scale (VAS) to measure the effectiveness of the treatment. The visual analog scale is a validated outcome measure has been used to measure the pain and it widely using in the researches. VAS is a measurement instrument for acute and chronic pain. It is a 10 cm line which represents range between two points (the left point is 0 cm that means no pain and the right point is 10 cm which means is the worst pain) and the score will be recorded by making a mark on the line and it interpreted as the patient's pain (**Delgado et al.,2018**).

Addition to that, the reliability of the VAS seems to be very high. Whereas, there are a studies confirmed that the VAS is adequately reliable for acute measurement (**Bijur PE et al.,2001**).

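### Two shock wave settings are compared on pain and function only: harms, tolerability and delivered treatment are recorded in no arm, because safety and full delivery are taken as given

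*Protocol*

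**What the plan says.** **Outcomes.** Sample size estimation sets the hierarchy: "Pain, considered the Primary outcome measure" and "Function limitation considered the secondary outcome measure". The Outcomes section describes two instruments, the Foot Function Index (FFI) and the VAS, and gives the purpose of the latter: "The pain will be assessed before and after the intervention by using visual analog scale (VAS) to measure the effectiveness of the treatment". The visit plan under Control group - C matches: "The pain and function improvement will be assessed before and after 6 sessions", with a further assessment at the end of week 12. Data collection adds a pain assessment after 3 sessions.

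**Safety.** Significance of the study states in the protocol's own voice: "Shockwave therapy is a safe and effective non-surgical treatment of plantar fasciitis comparing to other treatments". The Chapter II section on extracorporeal shockwave therapy adds, from one cited study, "no negative side effects have been reported from extracorporeal shock wave therapy".

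**Delivery.** Basic assumptions includes "All the subjects will receive the intervention as established" and also assumes that every subject attends the assessments.

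**Withdrawal.** Ethical consideration provides that the data of a participant who withdraws are left out of the research and destroyed.

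**Intended use.** Significance of the study hopes that the result will help physiotherapists adopt one specific protocol.

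**The concern.** The trial sets two active device settings side by side. They differ in frequency and pressure, so tolerability is a natural way for them to differ. Yet nothing in the plan would show such a difference. If one setting scores better on pain and function, the report could not say whether it was also harder to tolerate. Any statement about safety would come from the cited literature and not from the trial.

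The protocol gives reasons not to lean on that literature. Background says that most earlier studies were done "with no specific or fixed parameters set for the administration of the shockwave", so a general claim about shock wave therapy does not settle how these two settings compare.

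Delivery is a second gap. If a session is missed, shortened or run at a reduced setting, no planned record would show it. The pain and function results would then be read as the effect of the assigned settings, with no means of checking that patients received them.

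**Working it through.** There is no stated figure to reproduce: the protocol gives no sample size, effect size, dropout rate or adverse event rate. The check is a reading of the sections side by side, with simple arithmetic.

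**1. What is measured, and when**

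| Section | Measured | Timing |
|---|---|---|
| Sample size estimation | Pain (primary), function (secondary) | not given |
| Control group - C | Pain and function | before, after 6 sessions, end of week 12 |
| Data collection | Pain scores | before, after 3 sessions, after 6 sessions |
| Outcomes | FFI and VAS | VAS before and after |

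No section mentions adverse events, pain during application, the settings or impulses delivered, missed sessions, reductions, or reasons for stopping.

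**2. Can equal tolerability be presumed from the stated settings?**

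Time per session = impulses / frequency. Course total = impulses × 6 sessions.

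| Source | Group | Frequency / pressure | Impulses | Seconds per session | Course total |
|---|---|---|---|---|---|
| Intervention group A | A | 15 Hz / 3 | 1800 | 1800/15 = 120 | 10,800 |
| Intervention group B | B | 10 Hz / 4 | 1800 | 1800/10 = 180 | 10,800 |
| Chapter III, ESWT | study | 15 Hz / 3 | 1600 | 1600/15 ≈ 107 | 9,600 |
| Chapter III, ESWT | control | 10 Hz / 4 | 800 | 800/10 = 80 | 4,800 |

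Under either description the groups differ in pressure and in exposure time. Equal tolerability therefore cannot be read off the plan.

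**3. Is there one plan against which delivery could be judged?**

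No. The two descriptions disagree on impulses. Randomization & Allocation speaks first of two groups and then of three in a 1:1:1 ratio. Control group - C gives its patients sham shock wave therapy, while the Chapter III ESWT section gives a control group active settings. These passages must be reconciled. Until they are, a delivery record has no single reference.

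**4. What happens to a patient who leaves because of intolerance?**

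Under Ethical consideration, that patient's data are destroyed. The patient is then missing from the pain and function results, and no adverse event record exists to show why. If withdrawals of this kind are more common in one arm, that arm's results come from those who tolerated it.

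**5. How much could the trial say about safety if harms were recorded?**

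With zero events among n patients in an arm, the one-sided 95% upper limit for the event rate is 1 − 0.05^(1/n). Arm sizes are assumed.

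| n per arm | Upper limit |
|---|---|
| 15 | 1 − 0.05^(1/15) = 0.181 (18%) |
| 20 | 1 − 0.05^(1/20) = 0.139 (14%) |
| 30 | 1 − 0.05^(1/30) = 0.095 (10%) |
| 50 | 1 − 0.05^(1/50) = 0.058 (6%) |

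Without recording, no limit can be stated at any n.

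**The case against.** The strongest replies, and what stands of each:

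- **The side-effects sentence is literature review, not design.** This is true. The firmer basis is the protocol's own statement under Significance of the study and the delivery assumption under Basic assumptions. That heading may be customary in a thesis, but no other section checks what it assumes. Nor does the protocol say that outcomes were limited because safety was settled; that link is an inference.
- **A statistical analysis plan may cover it.** It could say how harms are analysed. What is collected at the sessions is a protocol matter, and an analysis plan cannot analyse data never gathered.
- **Small arms could say little about harms.** This stands. The limits above are wide, so a comparison between arms would be descriptive. That is a reason to report harms modestly, not to leave them unrecorded.

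Several stronger readings are tempting but unsupported:

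- A reader might infer that nothing is recorded during the six weeks of treatment. Data collection plans a pain assessment after 3 sessions, in which marked worsening of heel pain could show. It is still not a record of harm or delivery.
- A reader might infer that a protocol would be favoured on pain alone. Function is the secondary outcome and part of the hypothesis.
- A reader might infer that a patient given reduced treatment would be counted as fully treated. No analysis rule says so, and patients who withdraw are removed.
- A reader might infer that reductions would pull the two arms together and shrink their difference by a calculable share. Lowering the pressure in group A would move it away from group B. Lowering it in group B to 3 would still leave the frequencies different. Neither is a crossover to the other arm's settings, so no dilution figure follows.

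**Conclusion.** The concern holds in this form. The trial measures VAS pain and FFI function, takes safety and full delivery as given, and plans no record of harms, tolerability or delivered treatment in any arm. It could favour one setting on pain and function with no harm or tolerability data by arm, and it could not verify that the assigned settings were delivered. The withdrawal rule makes this worse, because patients who leave through intolerance disappear from the results.

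The size cannot be put as a bias, since no event rate, withdrawal rate or arm size is given. What can be stated is the limit on any safety claim: with complete recording and zero events, rates up to 18% (15 per arm) or 10% (30 per arm) would remain compatible with the data, on assumed arm sizes. The documents do not show that either setting is poorly tolerated, and the hypothesis is only that the protocols differ. The change should be made before enrolment, because unrecorded session data cannot be reliably recovered later.

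**What to change.** 1. Reconcile the group, sham and impulse descriptions (Randomization & Allocation and the three group sections against the Chapter III ESWT section), so that delivery can be judged against one stated plan. Which settings are right is for the investigators.
2. Make adverse events and tolerability a stated secondary outcome, reported by arm.
3. At each of the six existing sessions, complete a short form: any adverse event since the last session; pain during application; frequency, pressure and impulses delivered; and the reason for any reduction, missed session or stop. Repeat the adverse event check at the final assessment.
4. Replace the full-delivery assumption with a table of delivered treatment by arm.
5. Record withdrawals and their reasons by arm where consent allows, and align the wording under Ethical consideration.
6. Limit any safety conclusion to what the trial observed, with its interval.

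The cost is a few minutes per session, one extra table by arm and a wording change, with no new visits. One weakness remains. Blinding covers participants only, so the therapist who sets the device would also elicit the harms. The comparison between arms should therefore be presented as descriptive.

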## **CHAPTER III** **METHODOLOGY**

### **Subjects:**

Patients with PF will participate in this study and will be selected based on the following criteria:

### **Inclusion criteria:**

The patient will be included in this study if they meet of the following criteria

1. The participants should present with unilateral pain
2. The participants' age will be ranged from 20-50 years old.
3. The participants should have the pain from for at least 6 weeks.
4. Moderate disability as assessed by the foot function index (FFI)
5. The Body Mass Index (BMI) should be normal.
6. The participants should have pronated feet (6-9 on the foot posture index).

**Exclusion criteria:**

The patients will be excluded from this study if they meet any of the following criteria

1. History of surgery or fracture
2. History of corticosteroid injection within 6 months
3. Unable to follow or understand the instructions
4. High BMI
5. Sever foot pronation (+10 on the foot posture index)

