## **Randomization (Recruitment and allocation):**

### **Recruitment**

The patients with plantar fasciitis will be recruited from the Physical Therapy and Rehabilitation Center (out-patient) in Alain hospital, UAE. The purpose of the study will be explained to all participants before the start the assessment. A written consent forms will be signed after explanation.

Ethical approval will be obtained from education department of Alain hospital or from the University of Sharjah

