#### **Blinding:**

In this study:

- The participants will be blinded from the parameters of the intervention used.

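### Recent corticosteroid injection is an exclusion, but previous shock wave therapy, the treatment under test, is neither excluded nor recorded; the main risk is to the sham comparison, if a sham arm is kept

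*Protocol*

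**What the plan says.** The Exclusion criteria section of the Protocol opens with "The patients will be excluded from this study if they meet any of the following criteria" and lists five items: surgery or fracture, "History of corticosteroid injection within 6 months", inability to follow instructions, high BMI, and severe pronation. Previous shock wave therapy is not among them. The Inclusion criteria do not require patients to be new to it. They set a lower limit on symptom duration ("The participants should have the pain from for at least 6 weeks") and no upper limit.

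The Background, describing a cited comparative study, reports that "shockwave therapy given longer relief than the local corticosteroid injection". It gives no duration for either treatment.

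Patients are "recruited from the Physical Therapy and Rehabilitation Center (out-patient) in Alain hospital". Randomization & Allocation describes permuted blocks in a 1:1:1 ratio, with no stratification by earlier treatment. For the control arm the Protocol states: "This group will receive the same physiotherapy program in addition to sham shock wave therapy". The only blinding statement is "The participants will be blinded from the parameters of the intervention used". Pain (VAS) is primary and the Foot Function Index (FFI) secondary; the patient scores both. No section restricts or records earlier shock wave therapy.

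**The concern.** The plan screens out recent use of the treatment it reports as giving shorter relief. It leaves open recent use of the one reported as giving longer relief, which is also the experimental treatment. Someone who finished a shock wave course a few weeks ago and still has enough pain to qualify may be randomised to either active setting or to sham.

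Three things are at stake:

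- **Within-group change.** The Statistical method section plans paired t-tests in each group. Randomisation does not protect these, so a residual or fading effect of an earlier course enters the measured change directly.
- **Dilution.** Patients still in pain after a recent course may respond less to another, which would shrink the contrasts even if exposure is evenly spread.
- **Recognition of sham.** A patient who knows what real shock wave feels like may identify sham. Expectations then differ between sham and active patients, and both outcomes are self-reported. Randomisation does not remove this.

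Who may enter, and what is asked at screening, belongs in the protocol and is not something left to a statistical analysis plan.

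**Working it through.** The Protocol gives no sample size, effect size, standard deviation or share of previously treated patients, so there is no stated figure to reproduce. The check is first textual, then illustrative.

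**Text, side by side**

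1. Exclusion criteria: recent corticosteroid injection excluded; shock wave therapy not mentioned.
2. Inclusion criteria: no requirement to be new to shock wave therapy; no maximum symptom duration.
3. Background: shock wave relief reported as the longer of the two.
4. Chapter II, section on shock wave therapy: used in physiotherapy clinics, and preferred by clinicians before surgery, injections or steroid medication. With recruitment from a physical therapy outpatient centre, earlier exposure is plausible, but no rate is given.
5. Control group - C: sham. The Extracorporeal shockwave therapy section under Interventions instead gives the control group active shock wave at 10 Hz. These contradict each other and must be reconciled. The sham argument holds only under the three-arm description; the carry-over and dilution arguments hold under either.

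**Dilution (assumed inputs)**

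Let p be the exposed share, equal across arms in expectation, and suppose exposed patients gain nothing further (worst case). The mean contrast becomes (1 − p) times its value, and the sample needed for the same power rises by 1/(1 − p)².

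- p = 10%: contrast 90%; 1/0.9² = 1.23
- p = 20%: contrast 80%; 1/0.8² = 1.56
- p = 30%: contrast 70%; 1/0.7² = 2.04

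If exposed patients keep half the effect, the contrast is 1 − p/2. At p = 20% that is 90%, and the multiplier is 1.23, not 1.56.

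In patients per arm, with alpha 0.05 (stated; two-sided assumed), power 0.80 (stated) and assumed standardised effects d, n = 2(1.96 + 0.842)²/d²:

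| Loss of contrast | n per arm, d = 0.5 | n per arm, d = 0.8 | Power if n stays at 63, d = 0.5 |
|---|---|---|---|
| 0% | 63 | 25 | 80% |
| 10% | 78 | 31 | 71% |
| 20% | 99 | 39 | 61% |
| 30% | 129 | 51 | 50% |

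**Recognition of sham (assumed inputs)**

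If a share p of the sham arm recognises sham and rates pain 1.5 cm worse on the 10 cm VAS, the sham mean shifts by 1.5p: 0.15 cm at 10%, 0.30 cm at 20% and 0.45 cm at 30%, in favour of active treatment.

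**Net direction**

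The two mechanisms oppose each other. Let δ be the true active-versus-sham difference in cm. If the same share p is affected by both, the net error is 1.5p − pδ = p(1.5 − δ). It is positive when δ is below 1.5 cm and negative above. Since δ is not stated, the documents do not determine the sign.

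**The case against.** The strongest reply has five parts.

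- **The asymmetry is inferred.** The Protocol gives no reason for the corticosteroid exclusion and does not call it a washout; it might be there for safety. The Background sentence summarises one cited study. This stands: the document does not contradict itself here. The gap remains, because the experimental treatment itself goes unmentioned.
- **Carry-over contaminates every arm.** A reader might infer a systematic bias between arms. The documents do not support that. Allocation is randomised in permuted blocks, so exposure balances in expectation and what remains is noise, possible dilution and chance imbalance. Entry criteria also limit carry-over: Delimitation asks for moderate to severe pain and functional limitation, the Inclusion criteria for moderate disability, and Sample size estimation refers to a VAS of 4 to 10. A patient with large residual benefit would tend not to qualify.
- **The comparison of the two active protocols is compromised.** This too might be inferred, and matters because the Hypothesis concerns that comparison. But patients in both active groups receive real shock wave, and nothing suggests they would know which setting is expected to do better. Only dilution could touch it.
- **Previously treated patients are likely.** Recruitment names the clinic and nothing about treatment already given there. Exposure is plausible; its frequency is unknown.
- **Six months would be a sufficient window.** The Background gives no duration of relief, so the corticosteroid window sets a floor for consistency and does not show that the floor is enough.

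The reply narrows the harm considerably. It does not remove the omission or the risk to the sham blind.

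**Conclusion.** The point holds in limited form. Previous shock wave therapy to the affected foot is neither an exclusion nor a recorded item, so recently treated patients can enter any arm. The consequence most likely to bias a result is recognition of sham in the active-versus-sham comparison of VAS and FFI, and that depends on the sham arm surviving reconciliation with the section that gives the control group active treatment. Carry-over otherwise costs precision, may dilute the contrasts and distorts the paired within-group tests.

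No size follows from the documents. The exposed share, the lack of further response, the 1.5 cm reporting shift and the standardised effects are all assumptions. They show that the loss could range from negligible to material, and they do not estimate it. The change is worth making because it is cheap before enrolment and cannot be fully repaired later if the history was never collected.

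**What to change.** Add to the Exclusion criteria an item for previous shock wave therapy to the affected foot:

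- If a sham arm is kept, preferably exclude any previous exposure, since this also protects the blind.
- Otherwise, use a window that the investigators choose and justify, no shorter than the one already applied to corticosteroid injection, and record any earlier exposure at screening.

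Reconcile Control group - C with the Extracorporeal shockwave therapy section first, because the choice between these options depends on what the control group receives.

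The cost is one eligibility line and one screening question, asked alongside injection history. The recruitment pool becomes slightly smaller, and the results will apply to patients without (recent) shock wave therapy.
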